### Plans to give access to the full protocol, participant-level data and statistical code {31c}

After the publication of main and ancillary study outcomes in peer-reviewed journals the German version of the trial protocol, anonymized participant-level datasets and statistical codes can be obtained from the principal investigator upon personal written request.

## Oversight and monitoring

### Composition of the coordinating center and trial steering committee {5d}

The trial steering committee (TSC) designed the study and prepared and approved the final study protocol version (Version 1.3) as well as the amendments (Version 1.4 and 1.5). The TMC is responsible for patient recruitment, randomization, adherence to the protocol and CRF, correct acquisition of data/biological samples and their processing, for the reporting of severe adverse advents to the local REC, and for organizing TSC meetings and budget administration.

The data managers verify data and maintain trial IT systems including the online-based software REDCap® for randomization.

### Composition of the data monitoring committee, its role and reporting structure {21a}

In this single-center trial with a moderate total sample size and no planned interim analysis, a data monitoring committee was neither required by the TSC nor by the local REC.

### Adverse event reporting and harms {22}

In the current study protocol PPCs and PEPCs as potential intervention harms with a possible causal relationship are collected after patient enrolment and will be assessed as important clinical secondary outcomes (see {12}). Compound outcome and single PPCs/PEPCs analyses will be performed (see {12} and {20a}).

Intra- or postoperative death is defined as a severe adverse event and will be reported to the local REC. Additionally, all severe adverse events defined as study stop criteria and any protocol violations due to operational disturbances (see {11d}) will be reported and published along with the results of the main study.

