#### Important secondary outcomes of the main study

Oxygenation indices at different perioperative time points (Table 1, “art BGA”)Plasma IL-8 concentrations at different perioperative time points (Table 1)Perioperative ventilation pressures (mean and peak airway pressure, driving pressure), C_dyn_, airway resistances, and mechanical power of ventilation [26] up to 24 h after termination of CPBWeaning times from mechanical ventilationIncidence of postoperative pneumonias with the need of antibiotic treatment during the complete inpatient stay (suspected and/or confirmed, see below)Incidence of postoperative pulmonary complications (PPCs) during the first seven postoperative days including compound outcome analysis and single PPC analysis. PPCs encompass (modified from [20])New invasive ventilationNon-invasive ventilationPost-extubation respiratory acidosis (pH ≤ 7.3 and PaCO2 > 45 mmHg)ReintubationReadmission to ICU due to pulmonary reasonsMild hypoxemia defined as an PaO2/FiO2 < 300 but ≥ 200Moderate hypoxemia defined as an PaO2/FiO2 < 200 but ≥ 100Severe hypoxemia defined as an PaO2/FiO2 < 100Acute respiratory distress syndrome (ARDS) according to the Berlin criteria [27]Implantation of a veno-venous ECMOSuspected pneumonia defined as new pulmonary infiltrates plus 2 or more of the following clinical parameters: temperature > 38.5 or < 35.5°C, leucocyte count > 12 or < 4/nl and purulent secretions including antibiotic treatmentConfirmed pneumonia defined as pulmonary infiltrates and microbiological germ proof of tracheal aspirationsBronchoscopyPleural drainage due to pleural effusionsPleural drainage due to pneumothoraxIncidence of postoperative extra-pulmonary complications (PEPCs) during the first seven postoperative days including compound outcome and single PEPCs analysis. As PEPCs the following items are definedSepsis and septic shock (as defined in [28])Postoperative coronary interventionPostoperative wound infection with the need for antibiotic treatmentOther sites of infection with the need for antibiotic treatmentPericardial tamponade or other bleeding with intervention such as re-sternotomyImplantation of any device for extracorporeal life support (ECMO, Impella) or intra-aortic balloon pumpNon-pulmonary ICU readmissionAcute kidney injury with a Kidney Disease: Improving Global Outcomes (KDIGO) stage 2 or 3 [29]Postoperative delirium diagnosed by the Confusion Assessment Method for the ICU (CAM-ICU) [30]Systemic inflammatory response syndrome (SIRS) (according to [28]) free days during the first seven postoperative daysLengths of intensive/intermediate care unit stays and time to dischargeHospital readmission and mortality rate after one and 6 months post-surgery (Table 1, phone surveys)

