## Statistical methods

### Statistical methods for primary and secondary outcomes {20a}

The intervention group (perioperative individualized FCV) will be compared with best clinical practice PCV as the control group for all primary analyses. The primary study endpoint will be assessed with a linear regression model using the intervention group as an independent variable and the EuroSCORE II as an additional covariable. For all continuous secondary endpoints, similar linear regression models will be fitted. All binary secondary outcomes will be calculated using a logistic regression model as well as SIRS-free days using a Poisson regression model with the same independent variables. For the analyses of multiple secondary outcomes, the Bonferroni method for appropriate adjustment of the overall significance will be utilized.

For all confirmative statistical analyses, 2-sided *p*-values with a significance level of 0.05 will be utilized. *P*-values will be reported to four decimal places with *p*-values less than 0.001 reported as *p* < 0.001. All analyses will be conducted with the statistical software R (www.r-project.org, version ≥ 4.1.0).

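### Complications named as potential harms of FCV fall under the Bonferroni rule for secondary outcomes; with a family of about 10 or more tests, a large excess would usually be labelled not significant

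*Protocol article*

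**What the plan says.** Section {22} of the protocol article gives these complications a safety role: "In the current study protocol PPCs and PEPCs as potential intervention harms with a possible causal relationship are collected" after enrolment. In the same sentence they become efficacy-type endpoints, since they "will be assessed as important clinical secondary outcomes (see {12})." The next sentence fixes where the analysis rules are found: "Compound outcome and single PPCs/PEPCs analyses will be performed (see {12} and {20a})."

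Section {12} lists the outcomes. For the pulmonary family it reads: "Incidence of postoperative pulmonary complications (PPCs) during the first seven postoperative days including compound outcome analysis and single PPC analysis". The extra-pulmonary family is set up the same way.

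Section {20a} supplies the rules. "All binary secondary outcomes will be calculated using a logistic regression model", with group and EuroSCORE II as independent variables. For confirmatory analyses, "2-sided *p*-values with a significance level of 0.05 will be utilized". On multiplicity: "For the analyses of multiple secondary outcomes, the Bonferroni method for appropriate adjustment of the overall significance will be utilized." It does not say how many tests form the family, and it does not exempt outcomes that are read as harms.

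**The concern.** Bonferroni protects against false positive claims. That suits a claim that FCV reduces complications. For a harm the costlier error is a missed signal, and there the correction works in the unsafe direction: each outcome added to the list raises the bar that an excess under FCV must clear. Following {22} to {20a} leads to exactly this treatment, so the issue is a stated rule and not a detail left to an analysis plan.

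The setting gives the point weight. The Discussion says that the FCV arm deliberately sets aside the low-tidal-volume convention, and that this approach had so far been evaluated only pre-clinically. There is no interim analysis ({21b}) and no data monitoring committee ({21a}). Deaths, stop-criterion events and severe adverse events have their own reporting and review route ({22}, {23}). No comparable route is stated for PPCs and PEPCs, so their final comparison by arm carries much of the safety reading.

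**Working it through.** **Inputs from the article**
- Sample size {14}: 64 evaluable per arm, 70 randomised per arm.
- Two-sided alpha 0.05 ({20a}).
- Base rates (Background {6a}): any PPC about 50%; pneumonia below 5%, taken here as 5%.

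**Assumptions.** The article gives no size of excess and no m. I assume rises from 50% to 70% (compound PPC) and from 5% to 20% (pneumonia), and show a range of m.

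**The plan's own figure.** A two-sample t-test with d = 0.5, two-sided alpha 0.05 and power 0.80 needs 63.8, so 64 per arm (power 0.801). 128 × 1.1 = 140.8, which the article rounds to 140. The figure reproduces.

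**Family size, counted from {12}**
- m = 2: the two compounds only.
- m = 10: one test per top-level secondary outcome.
- m = 26: 15 PPC items + 1 compound + 9 PEPC items + 1 compound.
- m = 43: one test per listed outcome: oxygenation 1, IL-8 1, ventilation measures 6, weaning 1, pneumonia 1, PPC 16, PEPC 10, SIRS-free days 1, stays 2, readmission and mortality at two times 4.

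**Formula.** With n per arm, d = p2 − p1 and p̄ = (p1 + p2)/2:

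power = Φ[(d − z·SE0)/SE1], where z is the upper 0.025/m normal quantile, SE0 = √(2p̄(1 − p̄)/n) and SE1 = √((p1(1 − p1) + p2(1 − p2))/n).

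*Example, 50% to 70%, n = 70:* SE0 = 0.0828, SE1 = 0.0811.
- m = 1: z = 1.960; (0.20 − 0.1623)/0.0811 = 0.465; power 0.68.
- m = 10: z = 2.807; (0.20 − 0.2324)/0.0811 = −0.400; power 0.34.

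**Chance of flagging the excess, 64 to 70 per arm**

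| m | threshold 0.05/m | PPC 50% to 70% | pneumonia 5% to 20% |
|---|---|---|---|
| 1 (unadjusted) | 0.05 | 64-68% | 73-77% |
| 2 | 0.025 | 53-57% | 63-67% |
| 10 | 0.005 | 31-34% | 40-45% |
| 26 | 0.0019 | 21-24% | 29-33% |
| 43 | 0.0012 | 17-20% | 24-28% |

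**Limits at either side.** A rise from 50% to 65% is flagged only 40-43% of the time even without correction, and 13-15% at m = 10. A rise from 50% to 75% is flagged 84-87% unadjusted and still 55-60% at m = 10.

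**Check of the approximation.** Exact Fisher power at 64 per arm is lower. For 50% to 70% it is 59% unadjusted, 46% at m = 2, 26% at m = 10 and 16% at m = 26. The planned logistic model with EuroSCORE II would shift the figures somewhat.

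**The case against.** The strongest reply is that the loss depends on a number the article does not state. Defining the family is commonly left to an analysis plan, which is not shown. If only the two compounds counted, a rise from 50% to 70% would still be flagged slightly more often than not under the normal approximation. This stands as a limit on the size. It does not remove the point: {22} promises single-item analyses as well, and the absence of a harm exception is in the text whatever m is.

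Second, part of the low power is due to the sample size. This also stands, as the rise from 50% to 65% shows.

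Third, Bonferroni changes a significance label and does not suppress data. Compound and single-item results are promised, so an extreme split would be seen. It might also pass: 10 events against 0 of 64 (Fisher p = 0.0013) is significant for any m up to 37.

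Fourth, PPCs are legitimate benefit endpoints too ({7}), so controlling multiplicity over them is proper. That is agreed; the issue is only the harm reading.

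A reader might go further and infer that any real harm would be missed, that the trial has no other safety oversight, or that the authors will present non-significance as safety. The documents support none of these. Very large excesses remain detectable. Deaths go to the ethics committee, stop-criterion events are published with the main results, and the steering committee reviews stop criteria and severe adverse events at least every three months. No sentence says that a non-significant result will be taken as reassurance.

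**Conclusion.** The point holds in limited form. The article names PPCs and PEPCs as potential harms and routes them to a Bonferroni rule that has no exception for harms. For m of about 10 or more, an assumed excess such as 50% to 70% in any PPC, or 5% to 20% in pneumonia, moves from usually flagged (64-77% over both cases) to usually not significant (31-45% at m = 10, 17-28% at m = 43). At m = 2 the loss is modest.

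The result rests on the assumed excess rates, on a base rate of 50% for PPCs and 5% for pneumonia, on 64 to 70 patients per arm and on a simple two-proportion comparison. It concerns the significance rule and what a non-significant label can mean. It does not show concealment of harm or a general lack of safety reporting.

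**What to change.** State in {20a} and {22} that Bonferroni governs only claims of benefit on secondary outcomes. For the harm reading, report PPCs and PEPCs, compounds and single items, by arm with effect estimates and unadjusted two-sided 95% confidence intervals. Add that failing the Bonferroni threshold is not evidence of safety.

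The cost is about one sentence in each section and one table. Procedures, sample size and the primary analysis stay as they are. The downside is some false alarms: under no effect, 26 comparisons × 0.025 = 0.65 chance signals against FCV are expected. Such findings should therefore be labelled as signals and not as proof.

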### Frequency and plans for auditing trial conduct {23}

At least every three months during the patient enrolment period the TSC will meet together with members of the TMC in order to review the trial conduct with respect to protocol adherence and occurrence of stop criteria as well as severe adverse events. During these audits, every reporting and any protocol amendment to the local REC (see {25}) will be planned. Additionally, approved amendments will be made public to members of the TMC in written form.

### Plans for communicating important protocol amendments to relevant parties (e.g., trial participants, ethical committees) {25}

Modifications to the study protocol, which has been primarily approved by the local REC with respect to the primary and secondary outcomes, participant eligibility and exclusion criteria, sample size, application of interventions, and any other substantial changes to the protocol, will require an official amendment.

The amendment will be prepared and approved by the TSC and communicated to the TMC. After the reporting to the REC and the approval, modifications will be implemented and made public in the primary trial registry which for this study is the German Clinical Trials Register. This registry also allows for tracking the emergence of any amendments to the protocol.

Personnel changes or redistribution of responsibilities in the TMC with no effect on the study conduct are defined as minor administrative changes. They only need approval by the TSC which again may notify the REC.

### Dissemination plans {31a}

#### Primary outcome paper

After enrolment of the last study participant, the close-out of FLOWVENTIN HEARTSURG will be at the telephone interview 6 months post-surgery of this patient. From then onwards, we estimate 3 to 4 months for finalizing a manuscript about the primary and main secondary study outcome results for submission to an appropriate medical journal. The final manuscript version and the selected journal need the approval of the TSC and all co-authors before submission.

#### Publication of ancillary studies

After the acceptance of the main study paper, the results of ancillary studies are allowed to be published in peer-reviewed journals. Again, final manuscript versions and the selection of an appropriate journal need the assent of the TSC and co-authors.

#### Abstracts and presentations

Every doctoral candidate of the trial is supposed to submit one abstract with preliminary or final study results to an international or national congress before final data publication. Abstract contents need to be communicated to co-authors and the TSC and approved before being submitted.

If participants are willing to be informed about study results and consent to saving their personal email addresses, they will receive a copy of the publication(s) in case of open access.

## Discussion

During on-pump cardiac surgery procedures, lungs do not only need to withstand mid-term invasive ventilation in deep general anesthesia, surgical manipulations, and recurrent phases of apnea with consecutive atelectasis formation and atelectrauma. Lungs also receive a further hit by partial ischemia and reperfusion through the use of CPB, resulting in LIRI. These various injuries and their combination induce a pulmonary and systemic hyperinflammatory state [8, 37] which to a large extent accounts for the common postoperative pulmonary dysfunctions [10]. Clinical studies in the setting of cardiac surgery could demonstrate a reduction of key inflammatory biomarkers when lung protective ventilation strategies with respect to an open-lung approach [22] and combined with low tidal volumes [21] were applied perioperatively. However, the recent multicenter study PROVECS could not show a clinical benefit towards PPCs prevention when comparing a perioperative, generalized open-lung concept with common practice ventilation in cardiac anesthesia [9].

The trial scope of FLOWVENTIN HEARTSURG is to evaluate the new ventilatory mode of FCV in a single center RCT of a medium sample size in a perioperative approach. We did not exclude any preexisting patient comorbidities per se, except for situations with an initially modified (hyper-) inflammatory environment like in acute myocardial infarction and preexisting pneumonia as well as (suspicion of) endocarditis or intake of any preoperative immunosuppressive medication. The same open approach was chosen for the surgery: All types of single and combined surgical procedures with the exception of heart transplantation and assist device implantations are allowed as on-pump interventions. The reasoning behind this was to have a really thorough sample of cardiac surgical patients and procedures as the basis for our study. However, statistical analysis will adequately account for preoperative comorbidities and the severity of surgery as the EuroSCORE II will function as an additional covariable that specifically weighs patient-, cardiac-, and operation-related factors in the analysis of primary and secondary endpoints.

The comparator of FCV is PCV with a personalized PEEP and a DP mobilizing a lung-protective V_t_ of 6–8 ml/kg PBW. This ventilatory approach is in accordance with current national and international guidelines [38, 39] and large preceding and ongoing multicenter trials regarding perioperative individualization of PEEP [12, 20, 40]. For the titration of a C_dyn_-based best PEEP in the study protocol, an incremental PEEP trial is favored above a decremental PEEP trial as being less invasive due to no extensive airway recruitment with potentially detrimental effects at least in patients with ARDS [41]. PEEP is also titrated in the experimental group of FCV. The rationale behind a personalized PEEP is to exceed the lower inflection point of the static/quasi-static inspiratory lung pressure–volume curve in order to reduce the cyclic de-recruitment/atelectrauma [42, 43].

The theoretical lung protection considerations in FLOWVENTIN HEARTSURG differ from those in any other previous clinical trial: FCV application is not only individualized with respect to an open-lung approach regarding a patient-specific PEEP but also a personalized driving pressure (DP). The C_dyn_-based best DP is obtained during an incremental DP trial which will only be continued to the next DP level if V_t_ has increased disproportionately compared to the C_dyn_ on the previous DP level. This method shall prevent exceeding the upper inflection point of the inspiratory pressure–volume curve where lung compliance begins to decrease at high peak airway pressures resulting in at least regional lung tissue overinflation. With this approach the present theorem of lung-protective tidal volumes is deliberately disregarded as other determinants of mechanical power in the etiology of VILI are prioritized: the respiratory rate and airway flows [2, 43]. Through customization the DP in FCV, respiratory rate and airway flows can be reduced to a minimum still ensuring normocapnia, thereby reducing mechanical power and also dissipated energy of invasive ventilation [3, 4, 26]. Thus far, this approach has only been evaluated in a pre-clinical model of mid-term invasive ventilation resulting in better lung function and aeration compared to conventional PCV with protective tidal volumes and a fixed PEEP [4]. To our best knowledge, one other clinical trial also assesses the intraoperative application of FCV in the setting of cardiac surgery independently from our group [44]. However, the study focus is completely different to the perioperative approach of our study as the stated endpoints are only applicable to a short postoperative timeframe. On top of that the total sample size is rather low.

In order to adhere to the group-specific ventilatory protocols participants are accompanied by members of the TMC from in- to extubation. Preoperative PEEP and DP trials, the intraoperative period, and the postoperative individualization of ventilation are even always conducted by one anesthesiologist in both groups. This guarantees a maximum of uniform consistency in intervention application. From extubation onwards, assessors are blinded to interventions and any further medical therapy is at the discretion of the physician in charge. This approach also includes the handling of interventions classified as PPCs and PEPCs and therefore important secondary study outcomes. For example, in the case of postoperative hypoxemia, we did not define specific cut-off values or indications for non-invasive ventilation and this therapy will be decided upon the discretion of the medical doctor in charge. This might be a drawback in the study protocol as the variability in medical decisions might be increased.

Additionally, the study protocol includes the evaluation of perioperative lung aeration by electrical impedance tomography (EIT) embedded in an independent ancillary study of FLOWVENTIN HEARTSURG. EIT is a relatively new technique that allows for non-invasive point-of-care, two-dimensional visualization of air movements within the thoracic cavity without exposure to radiation. This allows for repetitive real-time assessments but implies a far lower resolution compared to current computed tomography analysis. EIT measurements can be performed on spontaneously breathing and mechanically ventilated patients which is the case in the study protocol. Half of the perioperative EIT recordings are under spontaneous breathing conditions (preoperative baseline and postoperatively after extubation as well as 24 h after CPB end) whereas the other half under invasive ventilation (after individualization of group-specific ventilatory settings preoperatively, after postoperative ICU admission and on pressure support ventilation during respiratory weaning). A similar perioperative approach of EIT measurements as in this study protocol has been recently published as a substudy of the PROVECS trial [33]. However, the authors focused on the results of only two EIT-derived parameters (dorsal fraction of ventilation and regional lung compliance) at four different time points up to the second postoperative day. The current study protocol comprises 5 numerical EIT-derived indices at 6 perioperative time points. With this approach, we hope not only to shed light on the effect of the interventions but also the course of respiratory “milestones” on the way through a cardiac surgery procedure and the subsequent intensive care period.

Regarding the echocardiographic evaluation of right ventricular function and pulmonary circulation, the respective substudy represents a nearly complete set of systolic right ventricular function parameters as described in the most recent guidelines for cardiac chamber quantification by echocardiography in adults by the American Society of Echocardiography and the European Association of Cardiovascular Imaging in 2015 [31].

With the study protocol of the main and ancillary trials, we hope to enable a holistic overview of the implications on lung function, aeration, PPCs, and PEPCs, as well as on cardiovascular side effects when ventilating on-pump cardiac surgery patients perioperatively with the new ventilation mode of FCV. The study FLOWVENTIN HEARTSURG is the largest clinical RCT on FCV thus far. The results of the application of individualized FCV compared to the best clinical PCV will be of high importance for our general understanding of perioperative invasive ventilation and the concomitant VILI.

